**Figure 1 Fig1:**
[figure not shown]
**Flowchart of study participation and interventions.**

### Randomization

During a physician- or nurse-led clinic visit in which a need for adjustment of loop diuretic (furosemide) doses is identified, the patient shall be tested for trial eligibility by the investigator. Patients who meet the eligibility criteria shall be invited to take part in the study, and those who accept will provide written informed consent. Clinical assessment and sociodemographic and clinical data collection shall take place before randomization. The investigator shall then report to the team member (not involved in the trial) in charge of the randomization list. Specific software shall be used for participant allocation into IG and CG by sequential random number generation.

### Sociodemographic and clinical variables

A structured questionnaire shall be administered to all trial participants for collection of data on sociodemographic and clinical parameters (age, sex, educational attainment, income, current prescriptions, comorbidities, smoking, alcohol intake, etiology of HF, duration of HF, prior admissions, echocardiographic findings, and serum sodium, potassium, urea, and creatinine levels). Weight, vital signs, presence of crackles, third heart sound, jugular venous distension, peripheral edema, history of orthopnea, hepatojugular reflux, hepatomegaly, and NYHA functional classification shall be assessed during the history and physical examination. Patients shall be instructed to measure their body weight daily, in the morning, after urination, while lightly clothed and before their first meal of the day. Patients will be required to use the same scale throughout the study period and calibrate (tare) it with 1 kg before body weight monitoring [17].

### Endpoints

The endpoints include hospital readmission and/or emergency department visits due to HF decompensation within 90 days, two-point change in CCS, and deterioration of NYHA functional class. The secondary outcome shall be a composite of the aforementioned primary endpoints and 90-day HF-related mortality.

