**Methods/Design:**

A PROBE (prospective randomized open blinded endpoint) parallel-group design will be used. Adult patients with a diagnosis of reduced ejection fraction HF, who are being treated at a specialized HF clinic are being recruited. Those with indications for loop diuretic dose adjustment during routine clinic visits will be randomized to take part in the trial. Participants in the intervention group (IG) shall have their diuretic doses adjusted in accordance with the AAD and receive four telephone calls (one per week) over 30 days to reinforce guidance on nonpharmacological management (fluid and sodium restriction). Participants in the control group (CG) shall have their diuretic doses adjusted by a physician during the first trial visit and shall not receive any telephone calls. Patients in both groups shall return at 1 month for face-to-face reassessment. The study endpoints shall comprise readmission and/or emergency department visits due to HF decompensation within 90 days and clinical instability. All participants shall be required to have a scale at home (or easy access to one), a telephone number, agree to telephone-based follow-up, and be available to return for a 1-month trial visit. Overall, 135 patients are expected to be enrolled in each group.

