### Inclusion and exclusion criteria

Adult patients with a diagnosis of reduced ejection fraction HF who are being treated at a specialized HF clinic are being selected. The diagnosis of HF is established by clinical history (signs and symptoms), echocardiographic findings (left ventricular ejection fraction <45%) [15] and medical records confirming management at the HF clinic. Patients are required to have a medical indication for adjustment of loop diuretic (furosemide) dose during a clinic visit, have a scale at home or ready access to one, have a telephone number for follow-up contact, agree to receive such follow-up and be available to return to the hospital for a 1-month reassessment visit. The exclusion criteria are communication barriers or physical impairments that preclude body weight monitoring, degenerative neurological conditions, waitlist status for cardiac transplantation, scheduled surgery and chronic kidney disease requiring renal replacement therapy.

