### Study protocol

Participants randomized to the CG shall have their diuretic dose adjusted at the physician’s discretion. These patients will not receive telemonitoring, but will return for 30-day clinical reassessment.

Participants randomized to the IG shall receive telemonitoring with the AAD for dose adjustment and CCS for assessment of signs and symptoms of decompensation and body weight fluctuations. Telephone calls shall take place once weekly for a total of four calls during the 1-month intervention period. First, the calling nurse shall enquire as to the presence of signs and symptoms of deterioration (paroxysmal nocturnal dyspnea, orthopnea, fatigue during activities of daily living (for functional class assessment), lower extremity edema, vomiting or diarrhea, dizziness or syncope, and body weight fluctuations) during the preceding week. Depending on the signs and symptoms reported, the patient shall receive guidance according to one of the following algorithm pathways: weight remained within the expected range (change in body weight <1 kg), weight loss was greater than expected (weight loss ≥1 kg), or weight gain was greater than expected (weight gain ≥1 kg). Guidance shall be provided in accordance with the patient’s individual needs regarding adherence to pharmacological and nonpharmacological management. A face-to-face reassessment shall be conducted at 30 days by a nurse blinded to group allocation. At each telephone contact/reassessment, the AAD shall be administered again to guide diuretic dose adjustment.

Data on clinical and sociodemographic parameters shall be collected from all participants in both groups, with the CCS used to assess clinical condition.

During clinic visits, all patients are provided routine guidance on HF, including information on pharmacological management (regular use of prescribed medications and their effects) and nonpharmacological management (weight management, fluid and sodium restriction, physical activity), and any questions they may have are answered.

At the 30-day visit, all patients shall undergo reassessment by means of the CCS and recollection of data on all variables of interest.

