At 90 days, the study endpoint (readmission or emergency department visit, change in CCS, deterioration in NYHA functional class, and HF-related mortality) shall be assessed by means of a chart review, consisting of an analysis of patients’ records. Patients who sought care at an outside facility shall be asked to provide their progress notes or discharge summary. Chart-based endpoints are expected to be confirmed by telephone contact with participants in both groups (Figure 1).

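### The CCS and NYHA endpoints have no fixed assessment time and no rule for patients already treated for an HF event, which dilutes the contrast between arms on both

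*Protocol article*

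**What the plan says.** The Endpoints section lists "hospital readmission and/or emergency department visits due to HF decompensation within 90 days, two-point change in CCS, and deterioration of NYHA functional class". Only the first item carries a time window, and the CCS item carries no direction. The section continues: "The secondary outcome shall be a composite of the aforementioned primary endpoints and 90-day HF-related mortality". The three items are therefore separate primary endpoints, and their union with HF death is the secondary outcome.

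The Study protocol section gives two times for the CCS and NYHA readings:

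- **Day 30.** "At the 30-day visit, all patients shall undergo reassessment by means of the CCS and recollection of data on all variables of interest". The examiner is blinded: "A face-to-face reassessment shall be conducted at 30 days by a nurse blinded to group allocation".
- **Day 90.** The items assessed then are "the study endpoint (readmission or emergency department visit, change in CCS, deterioration in NYHA functional class, and HF-related mortality", and the method is that they "shall be assessed by means of a chart review, consisting of an analysis of patients’ records", with confirmation by telephone.

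On the state of patients at entry, the Inclusion and exclusion criteria say: "Patients are required to have a medical indication for adjustment of loop diuretic (furosemide) dose during a clinic visit". The Randomization section puts the baseline assessment before allocation.

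The intention-to-treat sentence under Statistical analysis refers to patients who meet an endpoint before 90 days. It does not say what CCS or NYHA value such a patient receives.

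**The concern.** Readmission is an event, whereas CCS and NYHA are states read at one moment. A patient may decompensate, be treated in hospital and be read afterwards. Because everyone enters needing a diuretic adjustment, a patient recently decongested in hospital can plausibly score no worse than at baseline. That patient fails on readmission but is not deteriorated on the other two primary endpoints. A patient who has died has no reading at all.

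If the intervention prevents HF events, the control group holds more patients who are read after treatment. The CCS and NYHA comparisons then lose part of the benefit they are meant to show. The undirected CCS wording adds to the problem: read literally, a two-point improvement after an admission also meets that endpoint.

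**Working it through.** **Timing, side by side.** The Discussion lists the CCS components, among them crackles, jugular venous distension, third heart sound, hepatojugular reflux and peripheral edema. These need an examination. The one trial examination scheduled for both groups after baseline is at day 30. The day-90 assessment uses records and a telephone call, so it can take CCS and NYHA only from whatever visits the chart holds. The Endpoints section does not choose between the two times. If day 30 is meant, HF events in the first 30 days can precede the reading. If day 90 is meant, events over the whole 90 days can.

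**Size.** The article gives no expected rate for CCS or NYHA worsening and no control event rate, so there is no figure of its own to reproduce. The only planned effect is a 20% relative reduction in readmissions or emergency visits (Sample size section). All rates below are assumptions, and the CCS endpoint is taken as worsening.

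Notation:
- a = share with a treated HF event before the reading, in control (aC) and intervention (aI)
- w = share of those patients who still read as worse
- u = share of all other patients who read as worse, taken as equal in both arms

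Formulas:
- Worse as read: a·w + (1 − a)·u
- Worse with the event counted: a + (1 − a)·u
- Shift as read in favour of the arm with more events: (aC − aI)·(u − w)
- Contrast lost by not counting the event: (aC − aI)·(1 − w)

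Example at the planned 20% relative reduction, aC = 15%, aI = 12%, u = 20%, w = 0:
- As read: 0.85 × 0.20 = 17.0% vs 0.88 × 0.20 = 17.6%, which is 0.6 points the wrong way.
- Event counted: 0.15 + 0.170 = 32.0% vs 0.12 + 0.176 = 29.6%, a benefit of 2.4 points.
- Contrast lost: 3 × 1 = 3.0 points.

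| Events, control vs intervention | u | w | As read | Event counted |
|---|---|---|---|---|
| 15% vs 12% | 20% | 0% | 17.0% vs 17.6% | 32.0% vs 29.6% |
| 15% vs 8% | 20% | 0% | 17.0% vs 18.4% | 32.0% vs 26.4% |
| 10% vs 5% | 25% | 5% | 23.0% vs 24.0% | 32.5% vs 28.75% |
| 20% vs 10% | 25% | 5% | 21.0% vs 23.0% | 40.0% vs 32.5% |
| 30% vs 15% | 25% | 5% | 19.0% vs 22.0% | 47.5% vs 36.25% |
| 20% vs 10% | 25% | 25% | 25.0% vs 25.0% | 40.0% vs 32.5% |
| 20% vs 10% | 25% | 40% | 28.0% vs 26.5% | 40.0% vs 32.5% |

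The sign reverses only when w is below u. At w = u the contrast vanishes. At w = 40% the direction is right, but the benefit as read is 1.5 points against 7.5 with the event counted.

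**What offsets reversal.** In the 15% vs 12% example, reversal disappears if worsening among intervention patients without an event is at or below 0.170 / 0.88 = 19.3% instead of 20%.

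**The case against.** **The article does not fix day 30.** A reader might infer that CCS and NYHA are read at day 30 after every earlier admission has been treated. The text does not support this. It also places both readings at 90 days by chart review, and the CCS is used at each routine clinic visit, so a chart could record deterioration around an admission. Some patients will still be in hospital, or will have died. This objection stands, and it moves the fault to the unreconciled time. Neither time removes the gap in scoring.

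**Scoring after an intervening event is often left to an analysis plan, and this is a condensed article.** That is fair, and the missing rule alone would not be a finding. But the article itself states the endpoints with two conflicting times and no direction for the CCS change. Any repair of that definition has to say what counts as deterioration.

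**The admitted patient is counted elsewhere.** This also stands. Readmission or emergency visit within 90 days is its own endpoint and the one used for the sample size. The composite counts the patient whatever the later score. A reader might conclude that a null CCS or NYHA result beside fewer admissions could not be interpreted; with those two results available, that goes too far. Nor does the abstract define clinical instability as CCS and NYHA; that link is an inference.

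**The reversal is small and conditional.** It needs w below u and little benefit among patients without an event. At 17.0% vs 17.6% with 135 per arm, the standard error is √(0.170 × 0.830/135 + 0.176 × 0.824/135) ≈ 4.6 points, far above the 0.6-point shift.

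**Conclusion.** The point holds as a weakness in how two of the three primary endpoints are defined. Their assessment time is not settled between the Study protocol and Endpoints sections, the CCS change has no direction, and a patient treated for an HF event before the reading is not made to count as deteriorated.

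The dependable consequence is dilution. If the intervention reduces events and w is the same in both arms, the contrast lost is (aC − aI)·(1 − w), whatever happens among other patients. In the 15% vs 12% example that is 3.0 points.

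It is tempting to say that the arm with more admissions will look better. The documents do not support that as a prediction. It can happen, by about 0.6 points at assumed event rates of 15% vs 12%, or 1 to 3 points if event rates are halved, and only when treated patients score worse less often than others. The 90-day readmission or emergency visit endpoint and the sample size based on it are untouched.

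**What to change.** Make three changes to the endpoint definition:

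1. Reconcile the day-30 and day-90 statements to one assessment time for CCS and NYHA. Day 30 already has a blinded examination in both groups. Day 90 would need one, or a stated rule for which chart reading counts.
2. Define the CCS endpoint as a two-point worsening from baseline.
3. Class a patient with an HF admission, HF emergency visit or HF-related death before that assessment as deteriorated on CCS and NYHA. Report the scores as observed as a sensitivity analysis.

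The cost is a few sentences. Admissions, emergency visits and HF deaths are already collected by chart review and telephone. The Trial status section reports 66 patients enrolled and 58 completed, so the change should be dated and made without sight of results by group, and the completed patients classified by the same rule.

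The downside is overlap: CCS and NYHA would share events with the readmission endpoint and the composite, and so give less separate information. The observed-score analysis keeps that information visible.

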**Discussion:**

This trial shall assess the effectiveness of the AAD algorithm and non-pharmacologic management by early identification of clinical deterioration and establishment of a combined intervention to reduce emergency department visits, readmission rate, or a composite endpoint thereof.

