### Sample size

Sample size was estimated in the WinPepi 11.1 software suite, using readmission or emergency department visit within 90 days of randomization as the endpoint [16]. Considering a 20% relative reduction in readmissions or emergency department visits in the intervention group, a significance level of 0.05, a statistical power of 80%, and an attrition rate of 20%, the sample size was set at 270 patients (135 in each group).

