### Statistical analysis

Continuous variables shall be expressed as means and standard deviations if normally distributed or medians and quartiles otherwise. Categorical variables shall be expressed as absolute and relative frequencies. Depending on the distribution of variables, baseline characteristics and the effect of the trial intervention shall be compared by means of Student’s *t-*test or the Mann-Whitney *U* test (for continuous variables) or Pearson’s chi-square test (for categorical variables). A *P* value <0.05 (two-tailed) shall be considered statistically significant. Intention-to-treat analysis shall be employed for all patients who meet a trial endpoint before 90 days. All statistical analyses shall be carried out in Statistical Package for the Social Sciences (SPSS) 18.0.

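### Three endpoints are labelled primary and judged at one unadjusted 0.05, while the trial is sized on one; if any one counts as success, the false-positive risk is about 8–14%

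*Protocol article*

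**What the plan says.** All references are to the protocol article.

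- **Endpoints.** Three items are listed: "hospital readmission and/or emergency department visits due to HF decompensation within 90 days, two-point change in CCS, and deterioration of NYHA functional class". The next sentence fixes their status: "The secondary outcome shall be a composite of the aforementioned primary endpoints and 90-day HF-related mortality". The three are primary, in the plural, and the composite that adds HF death is secondary.
- **Sample size.** The calculation rests on one of the three, "using readmission or emergency department visit within 90 days of randomization as the endpoint". Its inputs are a 20% relative reduction, a significance level of 0.05, 80% power and 20% attrition, and its result is 270 patients (135 per group).
- **Statistical analysis.** One threshold serves all comparisons: "A *P* value <0.05 (two-tailed) shall be considered statistically significant". The section does not order the three primaries or divide the 0.05 among them.
- **Study protocol, 90-day assessment.** A single study endpoint is described with four components: readmission or emergency visit, change in CCS, NYHA deterioration and HF mortality. The CCS component has no two-point threshold here.
- **Abstract, Methods/Design.** The endpoints are summarised as "readmission and/or emergency department visits due to HF decompensation within 90 days and clinical instability".

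**The concern.** The endpoint that decides a trial, or the rule for combining several, should be clear before the data are analysed. Here three endpoints have equal rank, each can be tested at the full 0.05, and only one was considered when the trial was sized. Followed as written, the plan would permit a positive claim from a CCS or NYHA difference even if readmission or emergency visits showed nothing. The 5% and 80% in the Sample size section would then describe one of the three tests and not the conclusion of the trial.

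The 90-day paragraph adds to this. It gives mortality the same standing as the three primaries, and it leaves open whether any change in CCS counts or only a change of two points.

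**Working it through.** **The plan's own figure.** 135 per group less 20% attrition leaves 135 × 0.8 = 108 evaluable per group. The 135 cannot be reproduced, because no 90-day control event rate is stated. That is a separate question. What matters here is that the calculation uses one endpoint and the whole 0.05.

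**Inputs.** Three primary endpoints (Endpoints); two-sided 0.05 for each (Statistical analysis). The correlation between the test statistics is not given and is assumed to lie between 0 and 0.9. It should be positive, because the Discussion section says that the CCS also assesses NYHA class.

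**Case A: any one significant primary counts as success.** If the tests are independent, the chance of at least one false positive is

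1 − (1 − 0.05)³ = 1 − 0.857 = 0.143.

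For correlated tests, the rate comes from 1,000,000 simulated sets of three standard normal statistics, counting sets in which any |z| exceeds 1.96:

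| Assumed correlation | At least one false positive |
|---|---|
| 0 | 14.3% |
| 0.3, all pairs | 13.6% |
| 0.5, all pairs | 12.5% |
| 0.7, all pairs | 10.9% |
| 0.8, all pairs | 9.9% |
| 0.9, all pairs | 8.4% |
| 0.8 for CCS–NYHA, 0.3 with the event endpoint | 12.1% |
| 0.8 for CCS–NYHA, 0.5 with the event endpoint | 11.5% |

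**Case B: all three must be significant.** The false-positive rate cannot exceed 5%. Power is the chance that all three succeed together. If each had 80% power and the tests were independent, it would be 0.8³ = 0.512, about 51%. Positive correlation raises this, but it reaches 80% only if the three always succeed together. The plan states no power for CCS or NYHA.

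**Single primary.** One test at two-sided 0.05 has a 5% false-positive rate, and 135 per group is unchanged.

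**Three primaries with 0.05 divided equally.** Each is tested at 0.05/3 = 0.0167. The overall rate is 1 − (1 − 0.0167)³ = 4.9% if independent, and at most 5% under any correlation. An endpoint with 80% power at 0.05 then has power Φ(1.960 + 0.842 − 2.394) = Φ(0.408) = 66%. Restoring 80% multiplies the sample by (2.394 + 0.842)² / (1.960 + 0.842)² = 1.33. Taking 108 evaluable per group as the base, this is about 144 evaluable, or 144 / 0.8 = 180 per group and 360 in total.

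**The case against.** **No any-one rule is stated.** This is correct, and it makes the 8–14% conditional. Nor does the plan claim a 5% rate across the three endpoints; 0.05 is the level of each test.

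**A statistical analysis plan that is not shown may handle multiplicity.** It may, and the absence of an adjustment method from an article would not be a finding. But the article itself assigns primary status to three endpoints and sizes the trial on one. An analysis plan would have to choose among these statements.

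**Sizing on one endpoint is ordinary practice.** It is, and it suggests that readmission or emergency visit was meant to lead. The Endpoints section nevertheless gives the other two the same rank.

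**The abstract can be over-read.** Its Discussion speaks of a combined intervention "to reduce emergency department visits, readmission rate, or a composite endpoint thereof". A reader might infer that success on any of these would suffice, but the sentence describes what the intervention aims at and is not a success criterion. Likewise, clinical instability in the abstract need not be a competing endpoint. It can be read as an umbrella term for CCS and NYHA change, in line with the stated aim of improving clinical stability. The 90-day paragraph can be read partly as a list of what is to be ascertained. What remains is its singular study endpoint, the rank it gives mortality, and the missing CCS threshold.

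**The softer endpoints have some protection.** The design is PROBE, and the 30-day reassessment is done by a nurse blinded to allocation. Patients know their group, and symptoms such as orthopnea depend on what they report, so the protection is partial.

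**Conclusion.** The defect is real: three endpoints labelled primary, one unadjusted threshold, a sample size for only one of them, and a 90-day description that differs in the standing of mortality and the definition of CCS change. If any one significant primary is taken as success, the chance of at least one false positive is about 8–14% against the nominal 5%. If all three are required, the error rate is protected but power falls below 80%. On neither reading do the stated 5% and 80% both apply to the trial's conclusion.

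Two stronger readings are not supported. A reader might state a rate of 11–14% as a property of the plan. That needs both the any-one rule, which the article does not state, and correlations no higher than about 0.7. At 0.8 to 0.9 for all pairs the rate is 9.9% to 8.4%. A reader might also count the composite as a fourth primary test. The article makes it explicitly secondary, and it contains the three primaries, so it does not belong in the primary family and could not be independent of them.

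**What to change.** Before any outcome analysis:

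1. Name HF readmission or emergency visit within 90 days, the endpoint used for sizing, as the single primary, tested at two-sided 0.05.
2. Make the two-point CCS change, NYHA deterioration and the composite with HF mortality secondary.
3. Use the same list and the two-point CCS definition in the Abstract, the 90-day paragraph of Study protocol, and Endpoints. The Sample size sentence should carry the same HF qualifier as Endpoints.

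This needs no additional patients. It is a protocol amendment during recruitment: Trial status reports 66 enrolled, 58 of whom have completed. CCS and NYHA, which carry the clinical-stability aim, lose primary status. If the sponsor wants to keep them primary, a fixed testing order starting with the sized endpoint, or an equal division of the 0.05, would also control the error rate. Equal division costs about 14 percentage points of power per endpoint (80% to 66%) or about one third more patients.
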